#### Data collection

Data will be stored in the electronic health record. To protect participant confidentiality, only limited data (deidentified except for dates) will be used for analysis. Data will be exported and deidentified by the Center for Research Informatics before it is securely transferred to the research team for analysis.

#### Ethics statement and dissemination

This study was approved by the University of Chicago Biological Sciences Division Institutional Review Board (IRB24-0684). The study was registered on 2024-09-27 with clinicaltrials.gov (NCT06682468). Patients will be consented for participation. Data will not be shared because it includes dates and is not completely deidentified, in accordance with institutional policy. Results from the study will be disseminated through conference presentations, peer-reviewed publications, and community reporting.

#### Data safety and monitoring

A Data Safety and Monitoring Board (DSMB) will be formed to protect the safety of participants. The DSMB will evaluate the implementation of the trial, retention rates, patient safety, and maintenance of the integrity of data collection and management during this study. Any and all serious adverse events will be forwarded to the DSMB within 48 h of being recognized by study staff. The DSMB will have authority to recommend modifications to the clinical investigations or to stop these investigations if there are concerns with patient safety or the integrity of the study. The DSMB will meet every six months for the duration of the clinical trial.

### Data analysis

The intention to treat principle will be applied to all analyses (57). For all data we will use descriptive statistics to characterize and describe both the control and intervention arms. To confirm successful randomization, study arms will be compared with regards to age, sex and race/ethnicity distribution. Additionally, we will confirm that differences between the two arms do not exist for type of insurance and major comorbidities. If data is missing for variables under comparison to determine successful randomization, we will report the number of missing responses for each and show differences in between individuals with complete data and those with incomplete data across intervention arms, multiple imputation using the chained equations (MICE) method. Finally, logistic regression models will be used to adjust for baseline imbalances between groups. Comparisons will be made for categorical variables using a chi-square test or Fisher’s exact test, and for continuous variables, a two-sample t-test or Wilcoxon rank-sum test. We will use Bonferroni correction during our examination of baseline differences between treatment and control groups if analyses suggest differences between the groups, we will present adjusted model results rather than unadjusted results.

For primary and secondary outcomes that are proportions or binomial outcomes (percentage screened for SUD, number diagnosed with SUD, percentage diagnosed with SUD, number referred for SUD treatment, percentage referred for SUD treatment, HIV viral suppression, retention in care and kept visit proportion) a chi-square test or Fisher’s exact test and beta regression models will be used to compare the proportional outcomes in the trial arms. All significance testing will be two sided and use a level of 0.05.

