#### Implementation plan

We will inform all HIV clinicians (attending physicians, fellows, and advanced practice nurses) in the UCM Ryan White clinic about the study via email and at regular clinic meetings. Clinicians can opt-in to the intervention via email. Clinicians who do not provide assent will have their patients excluded from the RCT. Once launched, the ePORTAL HIV-S staff will meet regularly to monitor screening rates, discuss patient engagement, data collection, and identify issues related to workflow. We will provide feedback to clinical leadership and MAs regarding rates of screening and linkage to care (Table 1).

**Table 1 tab1:** Schedule of patient enrollment, interventions, and assessments for the trial period.

	Trial period			
	Enrollment		Post-randomization	Close out
Time point	-2 weeks to 0	0	1 to 12 months	12 months
Enrollment				
Eligibility screen	×			
Randomization	×			
Informed consent		×		
Intervention or comparator				
Population health SUD screening		×	×	×
Usual care SUD screening		×	×	×
Assessments				
Age, sex, race, ethnicity	×	×		
Number and percentage screened for SUD				×
Number and percentage diagnosed with SUD				×
Number and percentage reffered for SUD treatment				×
HIV viral suppression				×
Retention in care, kept visit propotion				×

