#### Intervention outcomes

The primary outcome is the percentage of PLWH who have had a clinic visit in the last two years in the Ryan White Clinic and who were screened for SUDs. Secondary outcomes include the number and percentage of PLWH diagnosed with SUDs, and the number and percentage of PLWH referred for SUD treatment. Secondary HIV care outcomes will include (1) retention in care measured as the kept visit proportion (the number of clinic visits attended divided by the number of clinic visits scheduled) in the 12 months after screening, and (2) HIV viral suppression, defined as a quantitative viral load <200 copies/mL in the year post-screening.

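### Viral suppression (secondary outcome): the stated adjustment rule leaves pre-randomisation suppression unused, at a cost in precision and interpretability, not validity

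*Protocol article*

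**What the plan says.** The Intervention outcomes section defines the secondary outcome as "HIV viral suppression, defined as a quantitative viral load <200 copies/mL in the year post-screening". Table 1 (Implementation plan) gives "HIV viral suppression" a single mark, in the 12-month close-out column. The only patient characteristics in its enrolment columns are "Age, sex, race, ethnicity".

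The Data analysis section names the baseline comparisons. First, "study arms will be compared with regards to age, sex and race/ethnicity distribution". Second, the team will confirm that "differences between the two arms do not exist for type of insurance and major comorbidities". It then says that "logistic regression models will be used to adjust for baseline imbalances between groups", and, after a Bonferroni correction of the baseline tests, that "if analyses suggest differences between the groups, we will present adjusted model results rather than unadjusted results".

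Viral suppression is among the outcomes for which "a chi-square test or Fisher’s exact test and beta regression models will be used to compare the proportional outcomes in the trial arms". No covariate is named for that comparison. Viral load or suppression before randomisation does not appear anywhere in the article as an eligibility criterion, stratum, baseline variable or covariate.

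**The concern.** Participants already receive care at the clinic and appear on its HIV registry (Selection/treatment of subjects), and the data come from the electronic health record (Data collection). Many should therefore have a viral load on record from before randomisation, although the article does not say so. Suppression before randomisation is likely to predict suppression afterwards.

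The article fixes a rule that would normally leave this information unused. A variable outside the list cannot trigger adjustment. Even if it were on the list, it would enter only after a significant corrected baseline test. A covariate earns its place by how well it predicts the outcome, not by a baseline p-value.

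Two things are at stake. The interval around the viral suppression difference is wider than the available data may allow. A single end proportion also mixes two processes: patients already suppressed can only maintain suppression, and the others can only gain it. An overall difference does not show which of these moved.

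**Working it through.** **The plan's own figure.** The article gives no rate, effect or power for viral suppression. Its one power statement concerns the primary outcome, and it reproduces. The rates are 0.80 × 0.60 = 0.48 and 0.48 + 0.52 × 0.40 = 0.688. With 440 per arm, 48% vs 69% and two-sided alpha 0.05, power is above 99.9%, against the stated 99%. This has no bearing on viral suppression.

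**Inputs.** From Sample size: about 440 per arm. Assumed, because the documents give none: 85% suppressed at follow-up, and a correlation φ of 0.4 to 0.6 between baseline and follow-up suppression.

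**Precision.**
- Unadjusted half-width: 1.96 × √(2 × 0.85 × 0.15 / 440) = 4.7 points.
- Adjustment multiplies the variance by (1 − φ²), which is 0.84, 0.75 and 0.64 for φ = 0.4, 0.5 and 0.6. The half-width multiplier is the square root.
- Adjusted half-widths: 4.3, 4.1 and 3.8 points.
- Equivalent gain in patients, 1/(1 − φ²) − 1: 19%, 33% and 56%.

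A simulation with binary data, comparing baseline-stratum standardised differences with raw ones, gave variance ratios that agree closely with this formula.

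**Power.** Normal approximation, two-sided 0.05, 440 per arm:

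| True rates | Unadjusted | φ = 0.4 | φ = 0.6 |
|---|---|---|---|
| 80% vs 86% | 66% | 74% | 84% |
| 85% vs 87% | 14% | 15% | 19% |
| 85% vs 86% | 7% | 7% | 8% |

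**Which row is plausible.** The planned screening contrast is 69 − 48 = 21 points. The Introduction puts substance use disorder at just under half of people with HIV. Taking one half, about 21 × 0.5 = 10.5% of the intervention arm would be additional positive screens. Suppose the effect on suppression runs only through them, with similar disclosure in both arms. A 6-point gain would then need 6 / 10.5 = 57% of them to be unsuppressed and every one to become suppressed. If 15% are unsuppressed, the ceiling is 10.5 × 0.15 = 1.6 points. If 30% are, it is about 3 points. The lower rows are therefore more realistic than the first.

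**Chance imbalance.** The standard error of the between-arm difference in baseline suppression is √(2s(1 − s)/440). This is 3.1 points at s = 70% and 2.0 points at s = 90% (s assumed). The listed checks would not look at it.

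**Interpretability.** Suppose 80% are suppressed at baseline, and in the control arm 95% of these stay suppressed and 40% of the others become so: 0.8 × 0.95 + 0.2 × 0.40 = 84%. Raising the second rate to 60% gives 0.8 × 0.95 + 0.2 × 0.60 = 88%. Raising the first to 100% instead gives 0.8 × 1.00 + 0.2 × 0.40 = 88%. The overall contrast is the same, with two different meanings.

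**The case against.** The strongest reply is that this is an omission from a condensed article. Covariates for one secondary outcome usually belong in the full protocol or analysis plan. Nothing in Data analysis forbids a baseline viral load, and the quoted list serves to check randomisation. Table 1 is no proof of absence either, since insurance and comorbidities are used at baseline without appearing in it. This stands to the extent that silence alone would be no finding. It does not cover the adjustment rule, which the article states. A plan that adjusted for baseline suppression whatever the balance would depart from that rule.

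A reader might infer more than the documents support:

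- *That the comparison is biased.* It is not. Randomisation keeps it valid, and chance imbalance is already reflected in its standard error.
- *That suppression is measured only at 12 months.* Table 1 suggests this, but the outcome definition gives a window of a year after screening. The single mark may only show when outcomes are tallied.
- *That the trial cannot separate patients already suppressed.* Records are exported with dates kept, so the split is probably feasible. It is simply not described.
- *That baseline suppression is the strongest predictor.* The documents do not rank predictors. Likely strong is as far as one can go.
- *That the trial gains substantial power here.* That needs an effect near 6 points, which looks optimistic beside a 21-point screening contrast. For effects of 1 to 2 points, power stays low with or without the covariate.
- *That the comparison is always raw.* Adjustment is planned, but only if imbalance is seen.

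**Conclusion.** The point holds as a matter of efficiency and clarity on one secondary outcome. Followed as written, the plan tests viral suppression without adjustment unless a listed variable appears imbalanced, and prior suppression is not listed. On the assumed 85% rate and correlation of 0.4 to 0.6, the avoidable width is about 0.4 to 0.9 points of a ±4.7-point half-width. The gain would be smaller with a weaker correlation or with many patients lacking a prior value. The case for the change rests on a tighter interval and a readable result more than on power. The primary outcome, the sample size and the validity of the randomised comparison are unaffected.

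**What to change.** 1. Add the last viral load before randomisation to the health record export, and show it in the enrolment column of Table 1.
2. Prespecify baseline suppression in three levels (<200 copies/mL, ≥200 copies/mL, none on record) as a covariate for the viral suppression outcome, included whatever the observed balance.
3. Report the standardised (marginal) risk difference with its 95% confidence interval. A logistic coefficient alone is a conditional odds ratio and does not deliver the risk-difference precision shown above.
4. Give suppression within each baseline stratum descriptively, without subgroup tests.
5. Reconcile the 12-month mark in Table 1 with the year-after-screening window in Intervention outcomes, and state whether the window runs from screening or from randomisation.

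The cost is one more export field and one model term, with no added visit or blood draw. The downside is that some patients will have no prior value; the third level keeps them in the analysis but adds little precision for them. The change should be fixed before any outcome comparison by arm, so that the covariate cannot look data-driven.

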#### Sample size

There are ~880 patients who will meet eligibility criteria; therefore, ~440 PLWH will be randomized to each arm. There is an approximately 80% retention in care rate in our clinic. For the usual care arm, based on the rates of depression screening at our clinic, we estimate the rate of in-clinic screening will be about 60%. For the intervention arm, we estimate that 40% of people will complete the portal screener, based on our data from the PORTAL-Depression study (56). Therefore, we anticipate the screening rates will be 48% in usual care and 69% in the intervention arm (Figure 2). Using a two-sided chi-square test to detect a difference in proportion between two independent samples, with an alpha of 0.05 we will have 99% power to detect this difference.

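### Retention and viral suppression, as defined, cannot be computed for every randomised patient, and who has a value can depend on arm, which conflicts with intention to treat for all analyses

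*Protocol article*

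**What the plan says.** In the protocol article, Data analysis states: "The intention to treat principle will be applied to all analyses". Its missing-data rule begins "If data is missing for variables under comparison to determine successful randomization" and goes on to counts, a comparison of complete and incomplete records, and chained-equations imputation. The next paragraph lists suppression and kept-visit proportion among the outcomes to be tested and gives no rule for patients without a value.

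Intervention outcomes defines retention as the kept-visit proportion, "the number of clinic visits attended divided by the number of clinic visits scheduled", taken "in the 12 months after screening". Viral suppression is "defined as a quantitative viral load <200 copies/mL in the year post-screening".

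Table 1, under Implementation plan, lists "Retention in care, kept visit propotion" and viral suppression, each marked only in the 12-month close-out column of a trial period counted from randomisation.

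Sample size supplies the rates used below: "There is an approximately 80% retention in care rate in our clinic" and, for usual care, "we estimate the rate of in-clinic screening will be about 60" per cent. It puts portal completion at 40% and anticipates screening of 48% and 69%, with about 440 patients per arm.

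**The concern.** Intention to treat needs an outcome that exists for each randomised patient, or a rule for those in whom it does not. These two definitions fail that in three ways.

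- A patient with no visit scheduled in the window has a kept-visit proportion of 0/0. A patient whom the clinic no longer schedules is poorly retained, yet gets no score.
- A patient with no viral load in the window has no suppression status.
- A patient who is never screened has no date from which either window can start. Being screened is the primary outcome, which the intervention is designed to change.

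The third is the most serious because it conditions a secondary outcome on a post-randomisation event that is expected to differ between arms. It also disagrees with Table 1: twelve months counted from screening end after the 12-month close-out for anyone screened after time zero.

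The Discussion says the approach may reach people who do not attend visits. If it does, the intervention arm will contribute values from less engaged patients whose counterparts in the control arm contribute none. An intervention that works as hoped could then appear to worsen suppression.

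**Working it through.** **1. Reproduce the plan's figures.** Inputs are from Sample size.

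- Control: 0.80 × 0.60 = 0.48.
- Intervention: 0.48 + 0.52 × 0.40 = 0.688, stated as 69%.
- Power for 48% vs 69%, 440 per arm, two-sided 0.05: above 99.9%, consistent with the stated 99%.

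These figures are not in dispute. They only size the affected groups.

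**2. Patients with no post-screening window.**

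- Control: 440 × (1 − 0.48) = 228.8, about 229 (52%).
- Intervention: 440 × (1 − 0.688) = 137.3, about 137 (31%).
- Patients with a window: about 211 control and 303 intervention.

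**3. Who the screened patients are.** This takes 80% retention as the share in care and applies 40% portal completion alike in and out of care, as the 69% figure implies.

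- Out of care: 0.20 × 440 = 88 per arm.
- Screened out-of-care patients, control: 0, since screening there happens only at visits.
- Screened out-of-care patients, intervention: 88 × 0.40 = 35.2, or 35.2 / 302.7 = 11.6% of those screened.

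**4. Effect on suppression if only screened patients are analysed.** Assumptions, not in the documents: suppression is 90% in care and s out of care, every screened patient has a viral load, and there is no treatment effect.

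- Control: 90%.
- Intervention: 0.90 × (1 − 0.116) + s × 0.116.
- All randomised, either arm: 0.80 × 0.90 + 0.20 × s.

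| s | Control, screened | Intervention, screened | Spurious difference | All randomised, both arms |
|---|---|---|---|---|
| 30% | 90% | 83.0% | −7.0 points | 78% |
| 50% | 90% | 85.3% | −4.7 points | 82% |
| 70% | 90% | 87.7% | −2.3 points | 86% |

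For scale, the standard error at s = 50% is √(0.90 × 0.10/211 + 0.853 × 0.147/303) = 2.9 points.

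**5. Moving the window to randomisation does not settle absent viral loads.** Assume 90% and 50% suppression as above, that all 88 out-of-care patients lack a viral load unless brought back, and that the intervention brings back 10% to 30% of them for testing and changes nothing else. True suppression is then 82% in both arms.

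- Observed values only. Control 90%. Intervention (316.8 + 8.8 × 0.5)/360.8 = 89.0%, to (316.8 + 26.4 × 0.5)/378.4 = 87.2%. Spurious harm of 1.0 to 2.8 points.
- Absent counted as not suppressed. Control 316.8/440 = 72.0%. Intervention 321.2/440 = 73.0%, to 330/440 = 75.0%. Spurious benefit of 1.0 to 3.0 points.

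The two rules err in opposite directions by similar amounts. Imputation from observed values lands near the first result unless its model captures engagement in care.

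**The case against.** The strongest reply is that rules for missing secondary outcomes are normally left to a statistical analysis plan or full protocol, neither of which is shown. That is right as far as it goes: the absence of a missing-outcome rule is not, on its own, a fault in this article. What remains is that the outcome definitions are stated here, and as stated they do not fit the analysis principle or the assessment time also stated here.

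A reader might go further in four ways that the document does not support.

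- *That the plan excludes out-of-care patients.* Nothing says so. Exclusion is what a chi-square test or beta regression does by default with an absent value, but it is an inference. The authors may intend the Table 1 time point to govern, in which case the 229 and 137 do not apply and the gap shrinks to patients with nothing scheduled or no viral load.
- *That 88 patients per arm will be missing.* The 80% is a clinic-wide retention rate used to project screening. A patient who misses scheduled visits scores 0, which is defined and appropriately poor, and one who disengages mid-year may have a viral load on file. Eligibility also requires an active portal account, and the Introduction links portal use to fewer missed appointments. The 88 is an indicative size for the out-of-care group.
- *That imputing baseline variables is pointless.* Data analysis provides for adjusted models when the arms differ at baseline, so imputed baseline values can enter the reported treatment comparison.
- *That counting an absent viral load as not suppressed cures the problem.* Step 5 shows that it can create a spurious benefit. The choice is a trade-off.

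The objection that the biases are modest and rest on outside suppression rates is also fair. At 2.3 to 7.0 points against a standard error near 3, they range from minor to enough to mislead.

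**Conclusion.** The point holds as a conflict within the article. Retention and suppression are defined over a window that starts at screening and on quantities that some patients will not have, while the analysis is declared intention to treat and the assessment is set at 12 months.

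Read literally, about 52% of control and 31% of intervention patients have no window, an imbalance produced by the intervention itself. Those counts follow from the article's own rates. The bias in suppression depends on assumed rates: 2.3 to 7.0 points of apparent harm under the range in step 4. How many patients will have no scheduled visit or no viral load cannot be derived from the document.

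The primary outcome is a recorded screen, so an unscreened patient counts as not screened. It and its power are unaffected. The matter concerns two named secondary outcomes and should be corrected before analysis.

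**What to change.** - Measure both outcomes over the 12 months from randomisation, with all randomised patients as the denominator, and align Intervention outcomes with Table 1.
- Beside the kept-visit proportion, add a binary retention measure defined for everyone: at least one attended visit in the window.
- Report by arm the number with no scheduled visit and the number with no viral load in the window.
- State in advance the rule for absent viral loads. Report suppression both with absent counted as not suppressed and with multiple imputation whose model includes arm, baseline viral load and prior attendance. Neither should stand alone, since the bias can run either way.
- Keep imputation of baseline variables where they enter adjusted models.

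The cost is revised wording and one or two extra analyses. Absolute suppression will look lower in the analysis that counts absent values as not suppressed; in the step 5 illustration it is 72% in the control arm against an assumed truth of 82%, so the text should explain that.

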## Discussion

PLWH are disproportionately affected by comorbid SUDs, which leads to negative health outcomes, potentiated by the fact that SUDs are underdiagnosed and often not treated among PLWH. Currently, limited evidence exists describing the optimal screening strategy for SUD among PLWH. Our approach will be one of the first to incorporate the privacy and convenience of a patient portal-based SUD screener compared to the current standard of care: in-person screening during routine clinic visits. Our method allows patients to self-report data, which then is automatically relayed to the patient’s primary HIV clinician, thus potentially increasing sensitivity of screening and both standardizing and improving documentation of screening results. Furthermore, we are screening for SUD among a population of PLWH who have historically received care at the clinic, as a population health approach, which differs from the reactive approach of screening during visits. This will allow the opportunity to reach PLWH who may not attend clinic visits. Also, because ePORTAL HIV-S is being implemented pragmatically within a large, real-world medical home, it allows us to test our intervention’s effectiveness and implementation strategy within the context of existing clinical practice. SUD remains one of the biggest challenges facing healthcare today, across diverse populations (15, 58, 59). We believe that the results of this study–and the fundamentals of ePORTAL HIV-S, including confidential, convenient online screening and incorporation of a CHW–will be potentially applicable to broader populations at risk for SUD. It will provide crucial information regarding the effectiveness of portal-based screening for SUD. Our findings may also have implications for screening for other behavioral or mental health conditions, or other conditions that may be associated with stigma.

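### The kept-visit comparison makes no use of pre-randomisation attendance, so its stated analysis forgoes precision the health record could supply at almost no cost; the primary outcome would gain little

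*Protocol article*

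**What the plan says.** All references are to the protocol article.

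- **Data analysis.** The arms are compared at baseline on age, sex, race/ethnicity, insurance type and major comorbidities. The section then says that "logistic regression models will be used to adjust for baseline imbalances between groups". Adjusted results replace unadjusted ones only if the baseline comparisons point to a difference. Outcomes that are proportions, including the kept-visit proportion, are compared by chi-square or Fisher's exact test and by beta regression, with no prognostic covariate named.
- **Intervention outcomes.** Retention in care is a secondary outcome, measured as the kept-visit proportion: "the number of clinic visits attended divided by the number of clinic visits scheduled", over the 12 months after screening.
- **Table 1 (under Implementation plan).** Demographics are the only assessments marked at baseline. The kept-visit proportion is marked at 12 months only.
- **Sample size.** "There is an approximately 80% retention in care rate in our clinic". This rate, multiplied by 60% in-clinic screening, gives the 48% expected in usual care.
- **Discussion.** One reason given for the portal is reach to patients who do not come to clinic: "This will allow the opportunity to reach PLWH who may not attend clinic visits".

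**The concern.** For an outcome that is a rate of behaviour over a year, the same rate over the preceding year is usually the strongest available covariate. Here it is on neither the list of baseline variables nor the assessment schedule. The rule for adjusting looks only at observed imbalance among the listed variables, so it would not bring attendance in even if the arms differed on it.

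The article states no power for the kept-visit comparison. Attendance also enters the primary outcome: in the sample-size model a usual-care patient who does not attend cannot be screened. What is at stake is precision, mainly for the kept-visit outcome, and not the validity of any planned comparison.

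**Working it through.** **Inputs from the article.** About 440 per arm ("There are ~880 patients who will meet eligibility criteria; therefore, ~440 PLWH will be randomized to each arm"); retention 0.80; in-clinic screening 0.60; portal completion 0.40; two-sided alpha 0.05 ("All significance testing will be two sided and use a level of 0.05").

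**Inputs assumed, because the article gives none.** The correlation r between prior-year and on-study kept-visit proportion, 0.3 to 0.6; the SD of that proportion, 0.30; the correlation phi between any prior-year attendance and in-trial attendance, 0.3 to 0.7.

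**1. The plan's own figures.**
- Usual care: 0.80 × 0.60 = 0.48.
- Intervention: 0.48 + 0.52 × 0.40 = 0.688, about 69%.
- Power for 48% against 69% with 440 per arm is above 99.99%. The stated 99% would need 198 per arm, so the claim that "we will have 99% power to detect this difference" is met with room to spare.

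**2. Kept-visit proportion.** Adjusting for the baseline value multiplies the variance by about (1 − r²). This is the linear-model approximation; beta regression is not expected to be identical.
- r = 0.3: 1 − 0.09 = 0.91, a 9% reduction.
- r = 0.6: 1 − 0.36 = 0.64, a 36% reduction.

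Difference detectable with 80% power = 2.80 × SD × √(1/n₁ + 1/n₂) × √(1 − r²).

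| Patients contributing | Unadjusted | r = 0.3 | r = 0.6 |
|---|---|---|---|
| 440 and 440 | 2.80 × 0.30 × √(2/440) = 5.7 points | 5.4 | 4.5 |
| 211 and 303 (screened only) | 2.80 × 0.30 × √(1/211 + 1/303) = 7.5 points | 7.2 | 6.0 |

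The second row is needed because the outcome is counted from screening. Read literally, only screened patients have it: 440 × 0.48 ≈ 211 and 440 × 0.688 ≈ 303. The proportional gain is the same in both rows.

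**3. Primary outcome.** Take a yes/no indicator of prior-year attendance with prevalence 80%, and keep in-trial attendance at the plan's 80%. At phi = 0.5, prior attenders attend again with probability 0.90 and the others with 0.40 (0.8 × 0.90 + 0.2 × 0.40 = 0.80).
- Control rates by stratum: 0.54 and 0.24. Intervention rates: 0.724 and 0.544.
- Unadjusted variance: (0.2496 + 0.2147)/440 = 0.001055.
- Within-stratum variances: control 0.8 × 0.54 × 0.46 + 0.2 × 0.24 × 0.76 = 0.2352; intervention 0.8 × 0.724 × 0.276 + 0.2 × 0.544 × 0.456 = 0.2095.
- The stratum differences, 0.184 and 0.304, have variance 0.0023.
- Adjusted variance: (0.2352 + 0.2095)/440 + 0.0023/880 = 0.001013.
- Reduction: 4.0%.

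The same calculation gives 1.4% at phi = 0.3 and 7.8% at phi = 0.7. If prior attendance predicted in-trial attendance perfectly, it would give 15.9%. The 95% CI half-width goes from 6.37 points to 6.24 (phi 0.5) or 6.11 (phi 0.7), against a planned difference of about 21 points.

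**The case against.** **This is analysis-plan detail.** Covariate choice is commonly left to a SAP, and an unadjusted comparison of randomised arms is valid. The second half stands: nothing planned is invalid. The first half does not dispose of the point, because the article itself fixes the list of variables, the trigger for adjustment and the assessment schedule, and prior attendance is in none of them. Reporting the primary result by prior attendance is an optional addition, not something the article had to contain.

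**The link from past to future attendance is assumed.** This stands. The 80% is a general clinic retention rate; the article does not describe it as each patient's prior-year attendance and gives no correlation. The gains therefore appear as ranges.

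**The kept-visit sample may be smaller.** This also stands, and the second row of the table allows for it. If only screened patients contribute, the arms are also selected after randomisation, which a baseline covariate does not cure.

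**Stronger readings that the article does not support.**
- *The primary outcome loses appreciable precision.* Only unscreened patients are eligible. If the planning rates had held in the prior year, prior attenders would be 32/52 = 62% of them. Re-attendance of 0.95 and 0.25 would then give an 11.3% reduction. But in-trial attendance would be 0.62 × 0.95 + 0.38 × 0.25 = 68%, with control screening at 41%, against the plan's 80% and 48%.
- *A chance attendance imbalance threatens the primary estimate.* With in-trial attendance held at 80%, an imbalance of 1.96 standard errors shifts the difference by about 1.3 to 1.8 points. The unadjusted confidence interval already allows for this.
- *The gain would be 16 points in attenders and 40 in non-attenders.* Those figures divide patients by on-study attendance. By prior-year attendance, with re-attendance of 0.90 to 0.95 against 0.25 to 0.40, the contrast is about 17 to 18 against 30 to 34 points.
- *The trial cannot examine reach to non-attenders.* Visits are in the health record and could be tabulated later; such an analysis is merely not named.

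**Conclusion.** The point holds for the kept-visit outcome. The stated analysis passes over that outcome's own baseline value, and the imbalance rule could not bring it in. The size depends on an unknown correlation: 9% to 36% of variance at r of 0.3 to 0.6, equal to a reduction in the detectable difference of about 0.3 to 1.2 points with all 440 per arm, or 0.3 to 1.5 points with screened patients only, at an assumed SD of 0.30.

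For the primary outcome the gain is small, roughly 4% to 8% of variance under the article's own rates at phi of about 0.5 to 0.7, and less if the correlation is weaker. Power is above 99.99% with or without adjustment, so no primary conclusion depends on it. The two outcomes should not be given equal weight.

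**What to change.** 1. Extract the visits scheduled and kept in the 12 months before randomisation for every randomised patient, and add this as a baseline item in Table 1.
2. In Data analysis, prespecify the baseline kept-visit proportion as a covariate in the kept-visit model regardless of observed imbalance. Give patients with nothing scheduled in that year their own category, since their ratio is undefined.
3. Optionally, adjust the primary comparison for any kept visit in the prior year (yes/no), reporting a standardised risk difference with its 95% CI. Also show the difference by that variable as a descriptive estimate with CI, which would speak to the aim of reaching non-attenders.

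The cost is one more field in the record extract and a few sentences of text, with no extra patients, visits or staff. The return on item 3 is small for the primary test. The covariate does not settle which patients count when the kept-visit period starts at screening; that definition needs its own clarification.
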